### Harms

2.22

During the study, local pain, swelling, distension, and itching may occur at the acupoint embedding sites, and adverse changes such as decreased appetite, diarrhea, and constipation may also occur (56–59).

To reduce these injuries, we will strictly screen participants before enrollment. If relevant symptoms already appear, we will systematically assess their severity: (1) If there is local redness and pain, no special treatment is required; keep the area dry, and if the pain is significant, cold compresses can be applied. (2) If local subcutaneous bleeding occurs, apply a cold compress to stop the bleeding, followed by warm compresses to promote bruise absorption. (3) If sutures are expelled, disinfect with iodine solution and avoid pulling them out by yourself; if accompanied by redness and swelling, medical treatment is required. (4) If local induration occurs, it often resolves on its own after surgery; if the induration continues to enlarge, medical treatment is necessary. (5) If allergic reactions or shock should occur, stop the experiment immediately and seek medical treatment as appropriate.

### Protocol version

2.23

The complete trial protocol (Version 1, dated August 20, 2025) is provided as a supplementary document with this submission and will be freely accessible in the published study protocol. If the protocol needs to be revised, the clinical trial registry will be updated to reflect the revision. The version control of the protocol document will be strictly maintained, and all participating sites will be required to use the most recent, approved version.

The main findings of this trial will be submitted for publication in a peer-reviewed scientific journal. Additionally, the primary results will be uploaded to a public clinical trial registry to ensure timely public access. To translate the research into practical benefit, a lay summary of the results will be prepared for trial participants and disseminated through relevant patient advocacy groups. Furthermore, the validated intervention protocol will be promoted through public health education and academic conferences.

## Discussion

3

Psoriasis is recognized as a systemic inflammatory disorder frequently exacerbated by visceral adiposity. Adipose tissue functions as a pro-inflammatory reservoir, secreting cytokines such as TNF-*α* and IL-6 that upregulate the Th17/IL-17/IL-23 axis (60, 61). Because traditional topical therapies fail to address this systemic driver, our trial employs a “double-hit” strategy via Acupoint Catgut Embedding (ACE). This approach aims to simultaneously resolve cutaneous lesions and underlying metabolic dysfunction, effectively disrupting the metabolic-inflammatory loop.

ACE is distinguished from manual acupuncture by its capacity for sustained stimulation. While manual needling provides only transient modulation, the embedding of absorbable sutures induces prolonged mechanical and chemical stimulation for up to 2 weeks, which is thought to be essential for remodeling chronic inflammatory and metabolic pathways (62, 63). This therapeutic effect is further directed by acupoint specificity; for instance, stimulation of ST25 (Tianshu) has been associated with the regulation of lipid metabolism in clinical studies (64–67). Such sustained, multi-target modulation addresses the crosstalk between immune and metabolic systems, where ameliorating insulin resistance and systemic cytokine loads is hypothesized to facilitate the resolution of psoriatic plaques (66, 67).

Compared with biological therapies, ACE represents a pragmatic, integrative option for specific patient populations. While IL-17 and IL-23 inhibitors are highly effective for moderate-to-severe psoriasis, their application in mild cases is often limited by cost–benefit considerations and regulatory indications. Additionally, evidence regarding the impact of biologics on metabolic comorbidities remains inconsistent across clinical trials. ACE offers a cost-effective alternative with a favorable safety profile, particularly for patients with mild psoriasis who are not candidates for systemic biologics but remain impacted by the inflammatory burden of excess body weight. By targeting both adiposity and systemic inflammatory markers, ACE provides a comprehensive management strategy tailored to this metabolic-cutaneous phenotype.

Our selection criteria were carefully dictated by both methodological rigor and ethical feasibility. We specifically enrolled patients with mild psoriasis (PASI < 3 or BSA < 3) because the trial design required a baseline topical treatment of only simple emollients (urea ointment). Excluding moderate-to-severe cases was an intentional ethical decision to avoid interfering with the intensive standard-of-care therapies those patients require, which would have confounded the specific therapeutic signal of ACE. Furthermore, the BMI inclusion threshold was set at ≥ 24 kg/m^2^ to ensure recruitment feasibility; a more restrictive cutoff (e.g., ≥ 30 kg/m^2^) would have unnecessarily limited the participant pool and underpowered the study without changing the underlying biological premise of metabolic-driven inflammation.

The methodological strengths of this trial are characterized by its multicenter framework and the implementation of specific protocols designed to mitigate performance bias—a persistent challenge in acupuncture-related blinding. By utilizing pre-loaded delivery devices and third-party randomization, we prioritized internal validity to ensure the reliability of the therapeutic signal. Beyond its rigorous design, this study addresses a significant gap in existing literature by incorporating an extended 32-week follow-up phase. This longitudinal perspective is essential for evaluating whether metabolic adjustments are sustained and how they influence long-term disease recurrence patterns. Furthermore, the integration of high-resolution molecular analyses—including single-cell sequencing and proteomics—allows for a granular investigation into the systemic crosstalk between metabolic health and cutaneous immune homeostasis. By moving beyond clinical observation, these exploratory findings may elucidate the biological pathways through which ACE modulates the psoriasis-obesity phenotype, offering a mechanistic foundation for integrative therapeutic strategies.

## Limitation

4

Although the PASI-based sample size calculation is more directly aligned with the primary endpoint of psoriasis, the absence of robust sham-controlled RCT data means that estimates derived solely from PASI assumptions, rather than BMI-based parameters, may still carry inherent uncertainty. Despite the use of a rigorous blinding design (such as sham embedding needles and independently prepared tool kits by a third party), potential bias from the operating physicians may still influence the results. In addition, although the sham embedding group simulated the needle insertion and pushing actions, there is an inherent difference from real embedding in terms of the physical stimulation of “thread implantation,” which may affect the equivalence of the placebo effect. We acknowledge the potential confounding effects of concomitant medications. Although we required patients to maintain stable regimens for underlying comorbidities throughout the trial, the complex interplay of medications commonly used in this population may still influence weight and inflammatory outcomes. As an exploratory trial, this study did not implement a drug washout period or perform subgroup analyses based on specific medication classes. Future studies should incorporate longer baseline observation periods or include medication usage as covariates to better delineate the treatment effect of acupoint catgut embedding. In addition, the primary endpoint of this study was set at week 8, with extended follow-up for secondary endpoints up to week 32. However, the sustainability of long-term efficacy after short-term intervention still requires further research, especially considering the chronic nature of psoriasis and the risk of weight rebound.

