### Rationale for the sham control

2.3

A sham procedure was selected as the control for the following reasons:

(1) *Methodological rigor*: As a double-blind, randomized controlled trial, a sham procedure is essential. It matches the verum ACE in all visible and sensory aspects, ensuring effective participant blinding and controlling for non-specific effects (e.g., placebo, natural disease variation). This allows for an objective assessment of the specific therapeutic efficacy attributable to the catgut embedding.(2) *Establishing clinical superiority*: Current standard treatments for mild psoriasis have limitations, including side effects and lack of efficacy for obesity. This trial aims to prove that ACE offers a specific therapeutic benefit, which necessitates comparison against a non-active intervention is necessary to establish its distinct clinical value and therapeutic advantage.

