### Sample size calculations

2.11

Based on our pilot data, the verum ACE achieved an improvement rate of 60%. Since no sham-controlled acupuncture trials for psoriasis are available, we derived the sham group response rate from the placebo effect observed in psoriasis pharmacological trials, which was approximately 25% as reported in the literature (40). Sample size estimation was performed using the standard formula for comparing two independent proportions (two-sided test, *α* = 0.05, power = 80%):

$$n1=n2=\frac{{\left(Z_{1-\alpha /2}+Z_{1-\beta }\right)}^{2}\times [p_{1}(1-p_{1})+p_{2}(1-p_{2})]}{{\left(p_{1}-p_{2}\right)}^{2}}$$

Where p_1_ = 0.60, p_2_ = 0.25, Z_1 − α/2_ = 1.96, and Z_1 − β_ = 0.84. The calculated sample size was 28 participants per group. After adjusting for a 20% dropout rate, the final sample size was determined to be 35 participants per group (total 70 participants).

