### Intervention

2.12

All participants will receive standardized baseline care. For skin lesions and xerosis, urea vitamin E cream (Fuyuan Pharmaceutical Co., Ltd., National Medicine Permit No. H34022160) will be applied as a moisturizer. Additionally, all patients will undergo health education regarding lifestyle and dietary modifications, along with training in daily skin care. To enhance adherence and objectively monitor compliance, researchers will add all participants to a WeChat health management group.

Participants will be instructed to photograph their daily meals; the images will be analyzed via a dedicated mobile application to estimate caloric intake. Daily step counts will be automatically recorded and tracked through the WeChat sports mini-program.

Throughout the trial, participants may continue their usual medications for comorbidities (e.g., diabetes, hyperlipidemia). We will require them to maintain the same types and doses of their underlying disease medications during the trial, with any changes in medication recorded at each visit. However, the use of any treatments specifically targeting psoriasis is prohibited.

(1) Experimental group:

In addition to conventional care, patients in the verum group will receive true catgut embedding acupuncture (needle insertion followed by thread embedding), at the following points: CV12 (Zhongwan), CV4 (Guanyuan), SP15 (Daheng), ST25 (Tianshu), ST36 (Zusanli), BL20 (Pishu), BL18 (Ganshu), and SP10 (Xuehai). All points are needled bilaterally except for CV 12 and CV 4. These acupoints were selected based on a comprehensive review of prior literature and established clinical expertise. This combination is designed to simultaneously address psoriatic inflammation and underlying metabolic dysfunction. Previous studies suggest that points such as ST25 (Tianshu), SP15 (Daheng), CV12 (Zhongwan), ST36 (Zusanli), and BL20 (Pishu) can help improve central obesity and gastrointestinal function (41, 42), while SP10 (Xuehai) is traditionally used to activate blood circulation and resolve stasis, and BL18 (Ganshu) is employed to promote blood circulation and regulate qi.

The acupoints were localized according to the World Health Organization Standard Acupuncture Point Locations. All acupuncture point locations are shown in Figure 2.

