(1) *BMI* (54): BMI will be calculated as weight (kg) divided by height squared (m^2^), following measurement of participants’ height and weight. BMI categories (kg/m^2^) are defined as: underweight (< 18.5), normal (18.5–23.9), overweight (24–27.9), and obesity (≥ 28).(2) *WC*: WC will be measured using a non-elastic tape. Participants will stand upright with feet 25–30 cm apart, weight evenly distributed, shoulders and abdomen relaxed, and breathing normally. The measurement will be taken at the midpoint between the lower margin of the last palpable rib and the top of the iliac crest (approximately 0.5–1.0 cm above the umbilicus), with the tape horizontal and snug but not compressing the skin. A WC of ≥ 80 cm in women and ≥ 85 cm in men will indicate possible abdominal obesity, while a WC of ≥ 85 cm in women and ≥ 90 cm in men will indicate central obesity.(3) *Hip circumference (HC)*: HC will be measured using a non-elastic tape. Participants will stand upright with feet together, arms at their sides, and breathing normally. The measurement will be taken at the point of greatest gluteal protrusion.(4) *WHR*: WHR will be calculated as WC divided by HC. Normal values are defined as ≤ 0.85 for men and ≤ 0.80 for women.(5) *Blood pressure*: blood pressure will be measured by trained medical personnel using a sphygmomanometer. The average reading from both arms will be recorded. Hypertension associated with obesity is defined as ≥ 140/90 mmHg. The types and doses of antihypertensive medications used by participants will be documented.(6) *Lipid profile*: laboratory analyses, including triglycerides (TG), low-density lipoprotein cholesterol (LDL-C), high-density lipoprotein cholesterol (HDL-C), and total cholesterol (TC), will be ordered by physicians and performed by the hospital laboratory. The types and doses of lipid-lowering medications used by participants will be recorded.(7) *Blood glucose*: laboratory analyses, including fasting blood glucose (FBG), glycated hemoglobin (HbA1c), and serum insulin, will be ordered by physicians and performed by the hospital laboratory. The types and doses of glucose-lowering medications used by participants will be recorded.(8) *Serum uric acid*: serum uric acid levels will be measured by the hospital laboratory. The types and doses of uric acid-lowering medications used by participants will be recorded.

3 Safety indicators and assessment methods

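### Drug use is already recorded and the authors recommend adjusting for it, but only in later studies; prespecifying baseline drug use as a covariate now would cost little and gain some precision, possibly very little

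*Protocol article*

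**What the plan says.** Section 2.12 (Intervention) of the protocol article allows background treatment: "participants may continue their usual medications for comorbidities (e.g., diabetes, hyperlipidemia". Regimens are to stay fixed, and any change is noted at each visit.

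Section 2.17 (Plans for assessment and collection of outcome) collects the detail by class. For glucose: "The types and doses of glucose-lowering medications used by participants will be recorded". For lipids: "The types and doses of lipid-lowering medications used by participants will be recorded". Equivalent statements cover antihypertensive and urate-lowering drugs.

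Section 2.21 (Statistical methods) analyses change in PASI and BMI with a linear mixed model and plans something similar for continuous secondary outcomes. It also lists t-tests and Mann–Whitney tests between groups. No medication covariate is named. The prespecified treatment interactions are with sex, age, baseline BMI and disease duration.

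Section 4 (Limitation) calls concomitant medication a potential confounder that could act on weight and inflammatory results even with stable regimens. It then says: "Future studies should incorporate longer baseline observation periods or include medication usage as covariates to better delineate the treatment effect of acupoint catgut embedding".

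**The concern.** The authors name a variable that may influence BMI, a co-primary endpoint, and say that including it would show the treatment effect more clearly. They leave that to someone else, although this trial's own case report forms will contain what is needed. No new visit, sample or participant is required.

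The arms are small (35 each), and section 2.2 names no stratification factor, so the share of drug users can differ noticeably between arms by chance. If users and non-users follow different 8-week courses, two things happen without the covariate. Part of an observed difference may reflect the mix of users, and the user/non-user variation stays in the error term. A reader who finds an imbalance in the baseline table will then raise the objection that section 4 itself raises, and an adjustment chosen after unblinding would be a weaker reply than a prespecified one.

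**Working it through.** **The plan's own figure.** Section 2.11 uses two-sided α = 0.05, 80% power and response rates of 0.60 and 0.25:

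n = (1.96 + 0.84)² × (0.60×0.40 + 0.25×0.75) / 0.35² = 7.84 × 0.4275 / 0.1225 = 27.36, rounded up to 28 per group. With 20% dropout, 28 / 0.8 = 35. Both stated figures reproduce. They concern a response rate, so the documents give no power for BMI or the laboratory outcomes.

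**Assumed inputs.** The documents give neither the share of users p of a drug class nor the user/non-user difference d in 8-week change (in residual SDs). Both are varied below.

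**Precision.** Without the covariate the variance is 1 + p(1−p)d² times the adjusted variance, so the gain in effective sample size is p(1−p)d².

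| p | d | p(1−p)d² | gain |
|---|---|---|---|
| 20% | 0.25 | 0.16 × 0.0625 | 1.0% |
| 40% | 0.25 | 0.24 × 0.0625 | 1.5% |
| 5% | 0.5 | 0.0475 × 0.25 | 1.2% |
| 10% | 0.5 | 0.09 × 0.25 | 2.3% |
| 20% | 0.5 | 0.16 × 0.25 | 4.0% |
| 40% | 0.5 | 0.24 × 0.25 | 6.0% |
| 20% | 1.0 | 0.16 × 1 | 16% |
| 40% | 1.0 | 0.24 × 1 | 24% |

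For a comparison of means that starts at 80% power with 35 per arm (a hypothetical starting point, equal to a detectable difference of 0.68 SD), a 1% gain gives about 80.4%, a 4% gain about 81.5% and a 24% gain about 87.7%. Going from one to four covariates changes power by about 0.1 percentage point.

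**Chance imbalance.** From the exact difference of two binomials with 35 per arm and p from 20 to 40%, the user shares differ by 10 points or more in 29 to 39% of randomisations, and by 20 points or more in 5 to 11%. The approximate 95% limit is 1.96 × √(2p(1−p)/35):

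- p = 20%: 1.96 × √(0.32/35) = 18.7 points
- p = 40%: 1.96 × √(0.48/35) = 23.0 points

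The resulting shift in the unadjusted difference, in total SDs, is imbalance × d / √(1 + p(1−p)d²):

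- p = 20%, d = 0.5: 0.187 × 0.5 / √1.04 = 0.09 SD
- p = 40%, d = 1.0: 0.230 × 1.0 / √1.24 = 0.21 SD

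For scale, the standard error of the difference is √(2/35) = 0.24 SD. Even these 1-in-20 shifts are smaller than one standard error.

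**The case against.** The strongest reply is that nothing here is invalid. Under 1:1 randomisation the comparison without a drug covariate is unbiased and keeps its type I error, and its standard error already allows for chance imbalance. That stands. Section 4's talk of confounding might lead a reader to infer that the BMI comparison is biased, but the design does not support that.

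The second reply is that the gain may be trivial. Outcomes are changes from baseline, section 2.12 requires stable regimens, and section 2.6 excludes recent significant weight fluctuation. A constant drug effect on level largely cancels in a change score, so a gap of 0.5 to 1.0 SD in change is optimistic. This also stands, and the lower rows of the table, at about 1 to 2%, are plausible.

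Third, a reader might infer that the authors excuse the missing covariates by calling the trial exploratory, and set that against section 2.3: "This trial aims to prove that ACE offers a specific therapeutic benefit". The text does not support this. In section 4 the exploratory label explains the absence of a washout and of medication-class subgroups. The covariate sentence follows separately and gives no reason.

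Fourth, covariate lists are commonly left to an analysis plan, and that plan is not shown. This would count if the article were silent. Here the article itself states the choice and places the adjustment outside this trial.

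**Conclusion.** The point holds as a low-cost improvement, not as an error that invalidates a result. The article recommends an adjustment that this trial can make from data it already collects, and defers it. The loss is some precision and some protection against chance imbalance.

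Its size rests on assumed values of p and d. It is about 1 to 2% of effective sample size if d is 0.25 SD, or if 5 to 10% use the class with d at 0.5 SD. It is 4% at 20% use and 0.5 SD. The 24% figure needs both 40% use and 1.0 SD, which stable regimens and change scores make unlikely.

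**What to change.** In section 2.21, prespecify before unblinding that baseline use (yes/no) of the relevant recorded drug class enters as a fixed covariate in the mixed models for BMI and the continuous metabolic and inflammatory outcomes. The minimum would be a prespecified sensitivity analysis with these covariates. Three details belong in the text:

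- Use baseline status only, because later changes in medication are post-randomisation.
- The investigators decide which class goes with which outcome. The documents do not settle this.
- Omit classes with too few users, under a rule set in advance.

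The t-tests and Mann–Whitney tests listed in 2.21 take no covariates, so the wording should tie the adjustment to the mixed models. Amend the sentence in section 4 that leaves medication covariates to later studies so that it agrees.

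Cost: a short addition to the analysis text, no new data or participants, and one degree of freedom per covariate. The gain may turn out negligible. The change concerns analysis only, not which drugs participants take.

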## Glossary

MetS: Metabolic syndrome
ACE: Acupoint catgut embedding
RCTs: Randomized controlled trials
DLQI: Dermatology Life Quality Index
PASI: Psoriasis Areaand Severity Index
BSA: Body Surface Area
VAS: Verbal Analogue Scale
WC: Waist circumference
BMI: Body Mass Index
WHR: Waist-to-hip ratio
PGA: Physician Global Assessment
ESR`: Erythrocyte sedimentation rate
CRP: C-reactive protein
HC: Hip circumference
LDL-C: Low-density lipoprotein cholesterol
BP: Blood pressure
TG: Triglycerides
HDL-C: High-density lipoprotein cholesterol
FBG: Fasting blood glucose
HbA1c: Glycated hemoglobin
ECG: Electrocardiogram
AEs: Adverse events
